#### ​Timeline

The total study duration will be 36 months to include 9 months for start-up, 20 months for the trial and 7 months for close down.

### Intervention

Sedation and ventilator weaning in standard care will follow current best practice; this is currently non-protocol-based and medically driven. Assessment and management of sedation and ventilator weaning will be according to usual practice. Sedation levels will be assessed and recorded with a validated sedation tool, and ventilator weaning will involve a slow reduction in ventilator support until low levels are achieved consistent with readiness for extubation.

The SANDWICH intervention comprises four components:

Greater interprofessional collaboration at ward rounds including review of COMFORT scores, sedative regimen and setting targets; and ventilation and setting ventilation goals.Sedation measurement using the COMFORT tool.Regular daily assessment of criteria for readiness to perform an SBT by bedside nursing staff.An SBT and if no distress, a discussion about the decision to extubate.

The intervention training will be delivered at sites by an implementation manager who will train the trainers (local champions, principal investigators and study-specific research nurses). Training will include an online course and face-to-face instruction. A full description of the intervention was available in the study-specific training manual that was only provided to PICUs during and after the training period to avoid influencing practice during the control phase. However, at the time of publication, we are now able to release full details of the intervention, which can be found at http://www.qub.ac.uk/sites/sandwich.

### Patients

All patients admitted to participating PICUs will be screened against the eligibility criteria.

#### ​Inclusion criteria

All children (<16 years) receiving IMV.

#### ​Exclusion criteria

Children not expected to reach the primary endpoint (tracheostomy in situ; not expected to survive; treatment withdrawal).Children who are pregnant, as documented in their medical notes.

#### ​Consent

A non-confirmed deemed consent (opt-out) approach will be taken in this trial. On patient admission, leaflets will be provided to parents or legal representatives informing them that the PICU is involved in a study and that staff will collect anonymised patient-level information. Leaflets will include contact details for more information or to request that their child’s data is not included in the analysis. Individual patient consent will not be confirmed with parents. This deemed consent approach is in line with guidance from the Ottawa Statement,^14^ feedback from proposed guidance on consent in cluster trials from the NHS Health Research Authority^15^ and was considered appropriate by parents and children during our feasibility work.^16^ Posters will be displayed in prominent areas to explain that a trial is taking place in the PICU.

#### ​Patient withdrawal

Children may be withdrawn from data collection on the request of parents or legal representatives. If parents opt-out from the study before data have been collected, this will be noted on the screening log, which will be held at the PICU. Following enrolment, if children are withdrawn, withdrawal will be recorded in the patient record and on PICANet. Data collected up to the point of withdrawal will not be included in the analysis.

### Outcomes

#### ​Primary outcome

The duration of IMV measured in hours from initiation of IMV (or admission if already intubated) until the first successful extubation (defined as still breathing spontaneously 48 hours following extubation).

#### ​Secondary outcomes

Incidence of successful extubation (defined as breathing spontaneously 48 hours following extubation).Number of unplanned extubations (defined as dislodgement of the endotracheal tube from the trachea, without the intention to extubate immediately).Number of reintubations.Total duration of IMV.Incidence and duration of postextubation use of non-invasive ventilation.Tracheostomy insertion.Postextubation stridor.Adverse events (eg, unplanned removal/dislodgement of vascular access or non-vascular catheters, bradycardia, hypoxia, cardiopulmonary resuscitation).PICU length of stay from admission to discharge (in days).Hospital length of stay from admission to discharge (in days).Mortality occurring within the ICU.Mortality occurring within the hospital.Cost per complication avoided at 28 days

Outcomes will be measured from patient admission up to 90 days or discharge (whichever is earlier). At the end of the 20-month enrolment period, data collection will continue for a maximum of 28 days.

### Data collection

The trial will collaborate with PICANet to make best use of the data collection infrastructure, which exists in PICUs in the UK. Participating PICUs routinely submit clinical data to PICANet to monitor activity and performance. PICUs have full access to and ownership of the data. Data are validated on entry and centrally on the PICANet server. PICANet produce a download facility that allows participating PICUs to extract data required for SANDWICH, thus reducing the burden of data collection for research staff.

When submitting individual patient data to PICANet, research staff will indicate enrolled patients by adding a unique trial number. PICANet has implemented a facility to allow research staff in each PICU to download a pseudoanonymised data set of their data for checking and upload to the SANDWICH Clinical Trials Unit (CTU) as required. This pseudoanonymised data set download will not include patient identifiable information. Trial data will be transmitted from participating PICUs to the CTU electronically using a secure method.

Outcome and compliance data that are not captured by PICANet will be collected and recorded on an electronic case report form (CRF) by PICU research staff and will not include patient identifiable information.

Table 1 shows the patient data collection schedule. The following data are collected:

Patient characteristics (eligibility, study number, intubation date/time, sociodemographics).

**Table 1 T1:** Patient data collection schedule

	Baseline (at point of recruitment)	Control phase up to 90 days or PICU discharge	Intervention phase up to 90 days or PICU discharge	Post PICU discharge
Patient characteristics	√			
Daily 8 am ventilator parameters		√	√	
Daily PCCMD		√	√	
Daily adverse events		√	√	
Outcomes		√	√	
2 hours prior to extubation, ventilator parameters and COMFORT score		√		
SANDWICH intervention checklist			√	
Hospital discharge and status				√

PCCMD, Paediatric Critical Care Minimum Data Set; PICU, paediatric intensive care unit; SANDWICH, Sedation AND Weaning In CHildren.

· Ventilator parameters (mode of IMV, fraction of inspired oxygen, positive end-expiratory pressure (PEEP), peak inspiratory pressure, ventilator rate, tidal volume and the level of pressure support above PEEP).

· Paediatric Critical Care Minimum Data Set.

· Adverse events

SANDWICH intervention data (readiness to wean criteria, COMFORT, ward round targets).Study outcomes.Post-PICU discharge (hospital length of stay, destination postdischarge, hospital mortality).

## Analysis

### Clinical evaluation

Baseline characteristics will be summarised by exposure and non-exposure to the intervention using summary statistics. PICUs will be classified as being exposed to the intervention on completion of the training period. The primary aim is to evaluate whether there is a difference in the duration of hours on ventilation before and after exposure to the intervention. We will use survival analysis (time to extubation) and estimate an HR for the intervention effect. This means that higher HRs will signify success of the intervention.

We will know exact survival times (ie, times until successful extubation) for most children, but children who die on ventilation, are transferred to another unit, are not weaned before transitioning to the training phase or are not weaned by 90 days will not have a known extubation time. We will treat such events as censored observations, making the assumption that children who are censored for any of these reasons will have an extubation time (ie, were or would have been removed from ventilation) greater than the time until they died or were transferred. These are plausible assumptions. In order to minimise any potential within cluster contamination, we will censor children when their PICU moves into the transition phase. When the PICU moves into the intervention phase, only new admissions will be included.

We will explore various models, but anticipate fitting a Cox proportional hazards model, perhaps with some treatment-by-covariate interaction to incorporate any non-proportionality. Allowance will be made for clustering using a frailty term for each PICU (this is similar to a random effect in a mixed-effects model). We will also adjust for calendar time, since the intervention is sequentially rolled-out. If a child is readmitted or transferred, they will be treated as new events and acknowledged within our analysis. Our primary estimate of the treatment effect will be a cluster and time-adjusted HR along with 95% CIs. Time adjustment is essential because this is a stepped wedge trial.

Secondary analysis will adjust for individual and cluster level covariates (such as the adherence score) and these will be prespecified. Null hypotheses and analyses for secondary outcomes take a similar form to that for the primary outcome. Where outcomes are not survival times, analysis will use the generalised linear mixed model, reporting risk differences for binary outcomes and mean differences for continuous outcomes (all adjusting for cluster and time effects).

Full details of the analyses will be given in the statistical analysis plan.

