#### ​Internal pilot study

An internal pilot in the first four sites randomised to the intervention will evaluate and report progress during the period from randomisation to training, during training and in the 8-week period after implementing the intervention. Specifically, the following criteria will be monitored:

Actual patient numbers/month of eligible children against predictions.Feasibility of data collection procedures.Percentage of parents opting out from allowing collection of their child’s data.Delivery of training (target >80% of staff/unit trained by the end of the pilot period).Adherence to intervention components (target >75% by the end of the pilot period).

We will address criteria not achieved in pilot sites through offering support and further training as required. The pilot report will be shared with all sites. The report will inform any actions required in trial management and training to address the above criteria for all sites.

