### Data analysis methods

Data from the PE will be analysed using the framework approach.^19^ A sample of textual data will be reviewed and double-coded by another independent member of the research team to ensure confirmability and trustworthiness. The integration of process and trial outcome data and subsequent analyses will be secondary and explanatory, and separate from the primary effectiveness analysis. The qualitative evidence will be systematically combined with outcome data to identify the processes mediating protocol implementation, receipt and setting and observed outcomes.

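### The secondary analysis names the adherence score, which arises after crossover, as a covariate for adjusting the treatment effect

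*Protocol article*

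**What the plan says.** Under Clinical evaluation, the primary result is defined without any adherence term: "Our primary estimate of the treatment effect will be a cluster and time-adjusted HR along with 95% CIs". The next paragraph adds: "Secondary analysis will adjust for individual and cluster level covariates (such as the adherence score) and these will be prespecified". The adherence score is the only covariate named, and the article does not define it.

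Other sections show what adherence refers to and when it is observed:

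- Internal pilot study, among the monitored criteria: "Adherence to intervention components (target >75% by the end of the pilot period".
- Data collection, Table 1: the row "SANDWICH intervention checklist" is ticked for the intervention phase and blank for the control phase.
- Data collection, list of items: "SANDWICH intervention data (readiness to wean criteria, COMFORT, ward round targets".
- Intervention, on standard care: "this is currently non-protocol-based and medically driven".
- Intervention, on the training manual: "only provided to PICUs during and after the training period to avoid influencing practice during the control phase".

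Under Process evaluation (Data analysis methods), the linking of process data to outcomes is described as "secondary and explanatory, and separate from the primary effectiveness analysis".

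**The concern.** A covariate that adjusts a treatment effect should not itself be changed by the treatment. Adherence to the SANDWICH components comes about because a PICU has been trained and has crossed over, and delivering those components is how the intervention is meant to shorten ventilation. A model with both the treatment indicator and adherence therefore splits the effect. The part that acts through adherence moves to the adherence coefficient, and the treatment coefficient keeps the rest.

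The article places the score among ordinary adjustment covariates, directly after the primary HR. A reader of the results could take the adjusted HR as a check on the primary one. If the coding makes the treatment coefficient refer to zero adherence, a real effect could seem to shrink on adjustment, or its interval could become too wide to use.

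**Working it through.** **Inputs from the article.** Sample size section: 28 patients per cluster per 4-week block, SD 9.6 days, ICC 0.005, exchangeable correlation, one cluster per sequence, difference 1 day, 5% significance (taken as two-sided), N = 9520, power about 80%. Design section: 8 weeks of baseline, one site crossing every 4 weeks, 8 weeks of training excluded per site, 8 weeks at the end with all sites exposed. Eighteen PICUs with two at one site give 17 randomised sites.

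**Inputs assumed.** Mean adherence 0.75 (taken from the pilot target) and between-PICU SD 0.05, 0.10, 0.15 or 0.20. The article gives no adherence distribution.

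**Step 1: reproduce the plan's figures.** There are 2 + 16 + 2 + 2 = 22 four-week blocks, of which each site contributes 22 − 2 = 20.

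- N = 17 × 20 × 28 = 9520, as stated.
- Cluster-period means have variance ICC·σ² + (1 − ICC)·σ²/m = 0.461 + 3.275 = 3.736, and within-cluster covariance ICC·σ² = 0.461.
- With fixed block effects, generalised least squares gives SE = 0.356 day for the treatment coefficient.
- Power = Φ(1/0.356 − 1.96) = 80.2%, matching the stated figure.

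**Step 2: raw score, zero in control blocks.** Let X be the treatment indicator and A the score. Half of the 340 cluster-blocks are control (170) and half intervention (170). With between-PICU SD s, corr(X, A) = 0.75/√(0.75² + 2s²). This is 0.996, 0.983, 0.962 and 0.936 for the four SDs. Adding A to the Step 1 model, averaged over 200 draws:

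| Between-PICU SD | SE of treatment coefficient (days) | Ratio to 0.356 |
|---|---|---|
| 0.05 | 3.15 | 8.8 |
| 0.10 | 1.58 | 4.4 |
| 0.15 | 1.13 | 3.2 |
| 0.20 | 0.91 | 2.6 |

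Other sets of draws agree closely, the lowest giving 0.87/0.356 = 2.4 at SD 0.20. With extra block-to-block variation of SD 0.03 within a site, the SE is about 2.4, 1.5 and 1.1 days for the first three SDs.

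**Step 3: what the coefficient then estimates.** Suppose a share q of a 1-day reduction acts through adherence, linearly. The effect in an intervention block is −(1 − q) − q·A/0.75. With X and raw A both in the model, the coefficient of X is −(1 − q): −1.00, −0.50 or 0.00 day for q = 0, 0.5 or 1. It is the effect at zero adherence, far from where units near the 75% target would lie.

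**Step 4: other codings.**

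- *Score centred on its intervention-phase mean, zero in control.* The coefficient becomes −(1 − q) − q·(0.75/0.75) = −1 for any q, the effect at mean adherence. The SE is 0.356 at every SD.
- *One constant per PICU, used in both phases.* The SE is about 0.358. The PICU effect largely absorbs the score, and the treatment coefficient changes little.
- *Score left missing in control.* A complete-case fit drops every control child, and no treatment effect can be estimated.

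**The case against.** The strongest reply is that the article does not say how the score is built or entered, and that the severe figures belong to one coding. This stands. The parenthesis follows directly on the words about cluster-level covariates, so one score per PICU is a natural reading, and Step 4 shows that it does almost no harm. The adherence mean is a pilot target, the SDs are assumed, and the calculation is linear while the planned model is Cox.

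It can also be said that absence of the score in the control phase is inferred. Table 1 schedules a COMFORT score before extubation in the control phase, standard care records sedation with a validated tool, and COMFORT measurement is one of the four components. Some component data therefore exist before crossover. Whether the score uses them is not stated, and nothing else in the article suggests a control-phase adherence score.

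The last reply is that covariates will be prespecified and details are left to the SAP. Definition and coding may indeed be left there, and their absence is no fault. But the article itself names this covariate, and prespecifying it does not turn a consequence of the intervention into a pre-exposure variable. The explanatory label in the process evaluation is not attached to this adjusted analysis. Nor does the harmless reading argue for keeping the score: a PICU constant that the frailty term absorbs adds little to the adjustment.

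**Conclusion.** The point holds for the secondary adjusted analysis only. The article plans to adjust the treatment effect for a variable that arises after crossover and, as far as the article shows, is recorded only in the intervention phase. This can take out whatever part of the effect acts through adherence. With a raw score set to zero in control, it also raises the SE about 2.5- to 9-fold under the assumed adherence distribution and the linear approximation. With a centred score or one constant per PICU there is little or no inflation.

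A reader might infer that the adjusted HR is bound to move to 1, or that it cannot be a treatment effect at all. The documents do not support that. A coefficient of zero needs both the raw coding and an effect wholly proportional to adherence, and the article commits to neither. Nor does it call this analysis a check on the primary HR. The primary HR, sample size and power are untouched, so this is a worthwhile correction to a secondary analysis and no threat to the trial's main result.

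**What to change.** Delete the parenthesis that names the adherence score, and state that the adjusted model uses only individual and cluster covariates fixed before exposure to the intervention. Analyse adherence separately, either as a dose-response analysis among intervention-phase children or as a complier-type analysis with its assumptions stated. Label it explanatory and do not report it as an adjusted treatment effect.

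The cost is about one sentence in the protocol, with matching wording in the SAP. No new data are needed, and the primary analysis does not change.

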### Economic evaluation

A cost-effectiveness analysis will be performed from the perspective of the hospital to estimate the cost per complication avoided at 28 days. The occurrence of respiratory complications at 28 days will be measured.

We will estimate total hospital costs until 28 days for each participant by applying appropriate unit costs from the NHS Schedule of Reference Costs^17^ to resource use data collected prospectively via the CRF or PICANet, as appropriate. Data on PICU resource use will be obtained via PICANet through the routine collection of the Paediatric Critical Care Minimum Data Set (PCCMDS). The PCCMDS consists of items recorded for each PICU bed-day that can be used to define the level of care and appropriate healthcare resource group. For patients discharged from hospital before 28 days, data on any PICU readmissions within 28 days will come from PICANet but data on readmissions to general hospital wards will not be collected. This is expected to lead to only minimal data loss, as the readmission rate within 30 days in a similar paediatric population was low (5%), with a mean hospital length of stay of less than 1 day.^18^

We will summarise hospital service use, costs and respiratory complications using descriptive statistics. Multilevel mixed-effects regression modelling will be used for total costs and respiratory complications. We will adjust for calendar time and clustering, ensuring consistency with the other models being constructed as part of the main analysis. We will estimate adjusted incremental (differential) total costs and adjusted incremental effects (respiratory complications). Standard methods will be used to explore and display uncertainty in the cost-effectiveness data including scatterplots on the cost-effectiveness plane and cost-effectiveness acceptability curves. Since there is no generally accepted threshold value for cost per respiratory complication avoided, a range of plausible thresholds will be explored. Sensitivity analysis will assess the robustness of the cost-effectiveness results to changes in key parameters. Since the time horizon of the analysis is less than 1 year, it will not be necessary to discount costs and effects.

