## Sample size

The primary aim of this study is to determine whether the intervention can reduce the average number of hours on ventilation in eligible children. To inform the power calculation, we used PICU admissions data for the years 2014 to 2016 from units participating in the trial to determine parameters to inform the sample size calculation. The expected sample size is 9520 based on an average cluster size of 28 patients per 4-week block. In this trial, duration of ventilation is censored at the point of transitioning from the control to the training period, discharge to another hospital, at 90 days, death and receiving a tracheostomy, so applying censoring to this data set provided us with a homogeneous population that more accurately reflected the trial population. The mean duration of mechanical ventilation was 5.8 (SD 9.6) days and an Intracluster Correlation (ICC) of 0.005 (95% CI: 0.001 to 0.01). It is postulated that a reduction of 1 day on ventilation is both clinically important and achievable. While our primary analysis will be a survival analysis, no methodology currently exists to determine power in a stepped wedge trial for this outcome type. We therefore determined the power available assuming a continuous outcome. This is expected to be a conservative approach meaning that it should have slightly underestimated the power not having allowed for the time to event nature of the data.

The cluster sample size app (https://clusterrcts.shinyapps.io/rshinyapp) was used to update the sample size calculation given this information. Using this app and for the actual design of the trial (using the actual information on the number of clusters and number of steps) and using the following assumptions: no. clusters per sequence=1, ICC=0.005 (with consideration across the range 0.001 to 0.01), an exchangeable correlation structure, mean difference=1, SD=9.6, at 5% significance level, the power is approximately 80% for a cluster size of 28 (figure 2).

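### The economic endpoint counts respiratory complications to 28 days, but the listed data collection records them only to PICU discharge, while hospital costs run to day 28

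*Protocol article*

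**What the plan says.** **Endpoint.** Secondary outcomes lists "Cost per complication avoided at 28 days". The Economic evaluation section repeats the horizon: "The occurrence of respiratory complications at 28 days will be measured". It also costs each child's hospital care until 28 days.

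**Collection.** In Table 1 (Data collection) the rows for daily adverse events and outcomes are ticked under two columns, "Control phase up to 90 days or PICU discharge" and "Intervention phase up to 90 days or PICU discharge". The only row ticked after PICU discharge is hospital discharge and status. The list in the text gives its content: "Post-PICU discharge (hospital length of stay, destination postdischarge, hospital mortality".

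**General follow-up rule.** Secondary outcomes says "Outcomes will be measured from patient admission up to 90 days or discharge (whichever is earlier". It does not say whether this is discharge from PICU or from hospital.

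**Missing data.** For children who leave hospital before day 28, the Economic evaluation section says that "data on any PICU readmissions within 28 days will come from PICANet but data on readmissions to general hospital wards will not be collected". It expects little data loss because readmission was uncommon (5%) and brief in a similar population.

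**The concern.** The 28-day endpoint and the collection schedule cannot both stand as written. Once a child moves from PICU to a ward, no listed item records a respiratory complication, yet the endpoint and the costs continue to day 28. The two halves of the cost-effectiveness ratio then cover different periods.

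Observation also stops at an event that the intervention is meant to bring forward, since a shorter PICU stay is one of the trial's objectives. If the intervention works, complications are observed for less time under the intervention. Ward events missed for that reason would count as complications avoided.

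The plan's argument that little is lost concerns readmission after the child has left hospital. It does not cover the ward part of the index admission.

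**Working it through.** The plan gives no figure for how much of the 28 days is observed, so there is none to reproduce on this point. Its sample size does not depend on it and is consistent: 17 sites × 20 observed four-week periods × 28 children = 9520.

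**1. The schedule, side by side**

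| Period | Respiratory complications | Hospital costs |
|---|---|---|
| In PICU, to day 28 | Adverse events and outcomes recorded (Table 1) | Counted |
| Ward, index admission, to day 28 | No listed item | Counted |
| PICU readmission after leaving hospital, to day 28 | From PICANet, presented as resource use | Counted |
| Ward readmission, to day 28 | Not collected | Not collected |

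**2. How much of the window follows PICU discharge**

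Inputs from the Sample size section: "The mean duration of mechanical ventilation was 5.8 (SD 9.6) days", and a target reduction of 1 day. PICU stay is not stated, so days in PICU after extubation, *e*, are an assumption, ranged from 0 to 10. The zero case is an extreme.

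Observed time per child is min(X + e, 28), where X is ventilation time. X is taken as lognormal or gamma with mean 5.8 and SD 9.6. Under the intervention the mean is 4.8 with the same coefficient of variation, so SD = 9.6 × 4.8/5.8 = 7.9.

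Lognormal case with e = 0:

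- σ² = ln(1 + (9.6/5.8)²) = 1.319, so σ = 1.148. For control, μ = ln 5.8 − σ²/2 = 1.098.
- E[min(X, 28)] = 5.8 × Φ((ln 28 − μ − σ²)/σ) + 28 × [1 − Φ((ln 28 − μ)/σ)] = 5.8 × 0.787 + 28 × 0.026 = 5.3 days.
- Unobserved share = 1 − 5.3/28 = 81%.
- For the intervention, the same formula with mean 4.8 gives 4.5 days, or 84% unobserved.
- Before rounding, the difference is 0.81 days and the ratio 0.847, so the window is 15% shorter.

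Across the range (lognormal / gamma where they differ):

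| Assumed PICU days after extubation | Control days observed | Unobserved, control | Unobserved, intervention | Days shorter | Relative |
|---|---|---|---|---|---|
| 0 | 5.3 | 81% | 84% | 0.81 / 0.76 | 15% / 14% |
| 2 | 7.2 | 74% | 77% | 0.79 / 0.73 | 11% / 10% |
| 5 | 10.1 / 10.0 | 64% | 67% | 0.76 / 0.68 | 8% / 7% |
| 7 | 12.1 / 11.9 | 57% | 60% | 0.73 / 0.64 | 6% / 5% |
| 10 | 14.9 / 14.7 | 47% / 48% | 49% / 50% | 0.69 / 0.57 | 5% / 4% |

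Only about 3% to 9% of control children would still be in PICU at day 28.

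**3. What this means for bias**

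The extra unobserved time under the intervention is 0.57 to 0.81 days, or 2 to 3 percentage points of the 28 days (0.57/28 = 2.0%; 0.81/28 = 2.9%). If ward complications occur at a daily rate *r* during that time, about 0.6*r* to 0.8*r* more events per child go unrecorded under the intervention. The protocol article does not give *r*, so the bias itself cannot be computed.

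**The case against.** **Late severe events are partly captured.** This stands in part. PICU readmissions within 28 days come from PICANet for children who had left hospital, and all PICU admissions are screened. But the plan presents these as resource-use data, and its Clinical evaluation section treats readmitted children as new events. Nothing says that a readmission counts as a complication of the index admission.

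**Fewer events on fewer ventilator days is a real benefit.** This stands. If complications arise mainly during ventilation or around extubation, a lower count per child is a treatment effect and little is missed. Only ward events are lost. For the same reason, a reader might infer from the change in mean ventilation (5.8 to 4.8 days) that recorded complications would fall by about 17% with no change in daily risk. That treats ventilation time as the observation window; the schedule observes children to PICU discharge.

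**Harm is assessed in other ways.** This stands. A reader might infer that the harm objective shares the 28-day endpoint. It has no time point, and the trial also records reintubation, unplanned extubation, post-extubation non-invasive ventilation, stridor and mortality in ICU and hospital. The 28-day mismatch belongs to the economic endpoint.

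**The article is condensed.** The definition of a respiratory complication may be in the full protocol. That is not the point made here. The article itself fixes a 28-day endpoint and a schedule that stops earlier.

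**Conclusion.** The mismatch holds as a contradiction within the protocol article. Followed as written, the plan would report a 28-day complication effect that its listed data do not observe in full, set against costs that do run to day 28.

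That contradiction needs no assumption; its size does. With 0 to 10 assumed PICU days after extubation, 47% to 81% of the control window is unobserved, and the intervention window is about 0.6 to 0.8 days (4% to 15%) shorter at the target effect. These figures also rest on the assumed shape of the ventilation times and on the same post-extubation stay for every child. A reader might state flatly that most of the 28 days is unobserved. The documents do not support that as fact, because PICU stay is not given and the share drops to about half at 10 days.

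The direction tends to favour the intervention. The bias may be small, since the difference between phases is under one day and the ward complication rate is unknown. The primary outcome and the power calculation are not affected.

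**What to change.** Reconcile Secondary outcomes, Table 1 and the Economic evaluation section around one window that the data can support:

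- Define and rename the effect measure as in-PICU respiratory complications up to day 28, plus PICU readmission with ventilation within 28 days.
- State that such a readmission counts towards the index admission for this measure, since the clinical analysis treats it as a new event.
- In the general follow-up rule, say which discharge is meant.
- State as a limitation that ward complications are not observed while costs run to day 28.

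This uses data the trial already plans to obtain, so the cost is rewording and a counting rule. The downside is a narrower endpoint.

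Adding a respiratory item to the hospital-discharge form is not advised at this stage. The protocol version shown is from March 2019, with data collection due to end in October 2019. In a stepped wedge, a late item would be filled mainly in intervention periods and would itself make ascertainment differ between phases. Rates per PICU-day are at most an optional supplementary description, because the intervention is meant to change that denominator.
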